### Primary and Secondary Outcome Measures

The primary outcome measure is the change in the 66-point FM-UE. The null hypothesis will be rejected when a statistically significant improvement between pre-intervention (T0) and the end of the cumulative treatment (T2) of at least 4 points is found. A medically clinically improvement difference (MCID) lower than the commonly used 5.25 point was chosen based on three current studies addressing the MCID (59–61). The three studies involve different stroke subgroups: chronic and moderately impaired (59), subacute and moderately impaired (60), and subacute and severely-to-moderately impaired (61). As suggested by (60), being in the chronic state makes the MCID drop significantly (5 vs. 9–11 points) and further reduction (around 2 points) is observed with severity. A lower MCID is also supported by (62) that suggests a decrease in the standard error in the reliability and validity of the FM-UE with severely affected subjects as there are less uncertainties when no movement can be performed.

Secondary outcomes look at the effectiveness of the two interventional phases separately and at the general benefit of the rehabilitation compared with the natural course determined from the waiting group; the latter is expected to be negligible in the chronic state. This comparison will be done through the clinical scales evaluated during the observational period of the waiting group. To evaluate if the recovery is long-lasting, all patients will be assessed on clinical scales (including FM-UE) 3-months after T2. Moreover, to study the underlying mechanisms of motor recovery during treatment, we will base our analyses on longitudinal multi-modal assessments data: motor and cognitive scales scores will be evaluated together with neural correlates from neuroimaging techniques including MRI and a combination of electrophysiological measures, as detailed above. Secondary outcomes also include safety, feasibility, and tolerability of the experiment.

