
With the AVANCER (*Accident Vasculaire cérébrale et Apport des Neurotechnologies individualisées chez le patient sévère Chronique: une Etude clinique prospective visant à Restaurer la mobilité du membre supérieur*)^1^ proof-of-concept trial, we propose a personalized neurotechnology-based therapy for upper-limb motor rehabilitation in severe chronic stroke patients. To maximize treatment effects, we propose two main pillars. The first is the combination of neurotechnologies to leverage their synergistic effects. The second is the personalization in the intervention duration and in a therapy assisted by a hierarchical sequence of non-invasive neurotechnologies, i.e., BCI, FES, exoskeleton and transcranial direct current stimulation (tDCS). To acknowledge high-dimensional heterogeneity in the investigated population (e.g., lesion location and dose-response) and because we expect no natural recovery, a within subject design is the most appropriate and has been chosen to evaluate the following hypothesis: the proposed cumulative neurotechnologies-based intervention leads to an increase of at least 4 points on the Fugl-Meyer assessment for the upper extremity (FM-UE) (35) on average across the targeted population, at end of the sequential treatment.

The main objective of AVANCER is to maximize upper-limb motor improvement in severely impaired stroke patients by the end of the cumulative tailored treatment. Secondary aims are to investigate the rehabilitation process in terms of time, intervention, and patients' specifics; and to determine underlying neural and clinically relevant behavioral mechanisms by means of a multi-modal evaluation. Moreover, given the novelty of the protocol, we aim to study the feasibility and safety of this setup and design.

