### Population Size

The study aims to recruit 40 patients, which by taking into account an estimated 20% dropout, leads to 30 patients completing the study with 10 starting in the waiting group (2:1 design). This number was obtained through an a-priori power analysis for sample size in G-Power (57) for a paired Wilcoxon Signed Rank test considering an alpha and beta of 0.05 and expecting an effect size of 0.64 (i.e., considering a mean FM-UE of 15, standard deviation of 4.7 (58) and expected improvement of 4 points). The sample size is also in agreement with previous neurotechnology-related studies and considering that the study is a proof of concept.

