### Statistics

To evaluate if significant motor improvement of the upper-limb is achieved, the FM-UE scores of all the 30 patients will be compared between the final (T2) and the initial (T0) evaluation visits: we will use a two-tail paired Wilcoxon Signed Rank test, with the probability value set at 0.05. The null hypothesis is H0 = “FM-UE scores at T2 and FM-UE scores at T0 follow the same distribution”, H1 = “FM-UE scores at T2 do not follow the same distributions of scores at T0; the distributions are significantly different”. H0 will be rejected if a *p-*value < 0.05 is obtained. This evaluation will be considered together with the expected four-point improvement on average.

To assess if the observed changes in the FM-UE are long-lasting, we will compare with the same test (Wilcoxon Signed Rank, alpha = 0.05) the FM-UE scores at T2 with those acquired at the follow-up (3 months after T2). Another related secondary outcome regards the validation of motor function stability of chronic stroke patients (i.e., no FM-UE improvement during the observation period). We will use a Kruskal-Wallis test with alpha at 0.05 to investigate differences in the FM-UE scores at the three time points of the observation period. We do not expect to reject the null hypothesis for which the three groups are said to come from the same distribution.

Among the most important secondary outcomes is safety and feasibility; for these, descriptive statistics will be provided. One major safety outcome is incidence of epileptic seizures during the intervention period with tDCS, as well as other SAEs. Furthermore, feasibility will be determined by the drop-out rate, usually in clinical trials set to up to 20%.

Important exploratory analyses will focus on the difference between the two interventional phases; such investigation might give an insight on the role of tDCS in the rehabilitation. To test the effect of dose and intervention type on the FM-UE we will use a mixed effects linear model with random effect of subject and fixed effects of session, intervention type and the interaction of the two. If significant results will be observed, we can then build on this initial model by adding more independent variables such as lesion location and time post-stroke. Other analyses will correlate the multimodal data acquired during the three full evaluations (T0, T1, T2), such as corticospinal tract integrity and the TMS evoked potential, with the clinical scales.

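### Two sections give different rejection rules for the primary null hypothesis (p<0.05 with a 4-point floor, or p<0.05 alone), and at the planned effect they disagree in about 41% to 49% of trials

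*Protocol article*

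**What the plan says.** Primary and Secondary Outcome Measures makes the change in the 66-point FM-UE the primary outcome. It ties rejection of the primary null to a significant result, worded as follows: "improvement between pre-intervention (T0) and the end of the cumulative treatment (T2) of at least 4 points is found". As written, that sets two conditions: significance and a gain of at least 4 points.

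Statistics defines the same null hypothesis as equality of the T0 and T2 score distributions. It names a two-tailed paired Wilcoxon signed-rank test and rejects when p is below 0.05, with no floor. It then adds: "This evaluation will be considered together with the expected four-point improvement on average".

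Population Size plans for 30 completers with a paired Wilcoxon test, "considering an alpha and beta of 0.05 and expecting an effect size of 0.64". The inputs named there are an "expected improvement of 4 points" and, "considering a mean FM-UE of 15, standard deviation of 4.7".

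The Introduction hypothesises that the intervention "leads to an increase of at least 4 points on the Fugl-Meyer assessment for the upper extremity (FM-UE") on average. The Abstract also states the four points as a hypothesis, and the Discussion sets them as the trial's MCID.

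**The concern.** A single primary null hypothesis needs a single rejection rule. Here a significant mean gain below 4 points is a success under Statistics and a failure under Primary and Secondary Outcome Measures. The sentence that brings the four points into Statistics does not say whether they are a condition, a benchmark or background. The verdict could therefore be settled after the data are seen. That matters more than usual because the primary comparison is an uncontrolled before-and-after one.

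The planned true gain and the floor are also the same number, 4. A rule that requires the observed mean to reach its own expected value is met only about half the time, so the power planned for the test does not carry over to it. In the other direction, a signed-rank test against no change can be significant at a mean gain well below 4, so a significant p-value does not by itself show a gain of at least 4 points.

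**Working it through.** **Inputs.** From Population Size: 30 completers, alpha 0.05, beta 0.05, effect size 0.64, expected gain 4, SD 4.7 given with a mean FM-UE of 15. From Statistics: a two-tailed test at 0.05.

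The SD of the T0 to T2 change is not stated directly, so two values are used, both assumptions:
- 6.25 = 4/0.64, implied by the stated effect size.
- 4.7, if the SD in Population Size is read as the SD of change. This gives 4/4.7 = 0.85, not 0.64.

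**Step 1: reproduce the plan's sample size.** Power uses the noncentral t for matched pairs with the Wilcoxon efficiency correction for a normal parent, 3/π:
- effective n = 30 × 3/π = 28.65
- noncentrality = 0.64 × √28.65 = 3.43
- one-sided 0.05: power 95.5%, and 30 is the smallest n that reaches 95%
- two-sided 0.05: power 91.1%, and 36 would be needed for 95%

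So 30 is reproduced, but only for a one-sided test of no change with no floor. Simulation of the two-sided test at SD 6.25 also gives about 91%. At SD 4.7 the two-sided power is about 99%.

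**Step 2: where the two rules separate.** The smallest significant mean is approximately t(0.975, 29) × SD/√30, with t = 2.045:
- SD 6.25: 2.045 × 1.141 = 2.3 points
- SD 4.7: 2.045 × 0.858 = 1.8 points

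A significant mean between roughly these values and 4 rejects under Statistics and does not reject under Primary and Secondary Outcome Measures.

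**Step 3: power of the rule with the floor at a true gain of 4.** When the true mean equals the cut-off and the changes are roughly symmetric, P(observed mean ≥ 4) = 0.50 for any n and SD. A mean of 4 is already well past the significance threshold, so the p-value condition removes almost nothing. Simulation at n = 30 with a two-sided signed-rank test gave 49% to 50% at SD 6.25 and 50% to 51% at SD 4.7.

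**Step 4: how often the verdicts differ.** Disagreement = P(significant) − P(significant and mean ≥ 4).

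| SD of change | p<0.05 alone | p<0.05 and mean ≥ 4 | Opposite verdicts |
|---|---|---|---|
| 6.25 | 91% | 50% | 41% |
| 4.7 | 99% | 50% | 49% |

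**Step 5: true gain needed if the floor stays (SD 6.25).** For 95% probability of an observed mean of at least 4: 4 + 1.645 × 1.141 = 5.9 points. For 80%: 4 + 0.8416 × 1.141 = 5.0 points.

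**Sensitivity.** Primary and Secondary Outcome Measures does not say that the floor applies to the mean. If it applied to the median of whole-number changes, the power of the rule would be about 58% to 64%, still far below 95%.

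**The case against.** The strongest reply is that the document can be read as one plan. Statistics is where the formal hypotheses, test and threshold stand, and it calls the four points expected. The Discussion makes them the MCID. On that reading the trial has a significance test plus a benchmark of clinical relevance, and the only defect is one loosely worded sentence. This is a sensible reading, and the fix below adopts it. But that sentence is itself a rejection rule, and the linking sentence in Statistics does not settle the role of the four points.

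Three parts of the defence stand.

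- A reader might infer that the power calculation is wrong and that the trial really has 50% power. The document does not support this. Population Size attaches its beta to the Wilcoxon test, not to a test plus a floor. The 50% applies only if the rule with the floor governs.
- A reader might count the Introduction and Abstract as further competing success rules. They state a hypothesis about the gain and set no decision criterion.
- The 50% is a general property of any floor set at the planned effect. Requiring the estimate to reach the target can be a deliberate choice in a proof-of-concept trial, provided its power is stated.

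A reader might also take the rule with the floor as a formal test against a 4-point null, where power at a true gain of 4 would be only the type I error rate. The null hypothesis in Statistics is equality of distributions, so that reading is not supported either.

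**Conclusion.** The contradiction between Primary and Secondary Outcome Measures and Statistics is real and affects the primary conclusion. At 30 completers and a true gain of 4, the two rules give opposite verdicts in about 41% of trials (SD of change 6.25) to 49% (SD of change 4.7). If the floor governs and applies to the observed mean, power is about 50% regardless of SD.

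These figures assume roughly normal, symmetric changes. The 41% to 49% depends on the assumed SD; the 50% does not. The test, time points, alpha and estimate are the same under either section. What is undecided is whether a given result counts as success. Adopting the p-value rule does not recover the planned 95% either: with the two-tailed test it has about 91% at effect size 0.64.

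**What to change.** Use one rule in both sections, fixed before the analysis.

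- **Primary and Secondary Outcome Measures:** delete the 4-point condition from the rejection sentence. Reject the null hypothesis of no change from T0 to T2 at two-sided p<0.05 with the change in the direction of improvement.
- **Statistics:** replace the linking sentence with a statement that 4 points is a benchmark of clinical relevance, reported beside the mean change and its 95% CI. Add that a significant result alone will not be reported as showing a gain of at least 4 points.
- **Population Size:** state the power of the two-sided rule as about 91% at effect size 0.64 and 30 completers.
- **If the sponsor prefers to keep the floor as a success condition:** write it into both sections, say that it applies to the observed mean, and state its power as about 50% at a true gain of 4.

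The Introduction and Abstract state the hypothesis and need no change as decision rules. The cost is a few sentences and a less favourable power figure. No extra patients, data or tests are needed.

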### Statistics

To evaluate if significant motor improvement of the upper-limb is achieved, the FM-UE scores of all the 30 patients will be compared between the final (T2) and the initial (T0) evaluation visits: we will use a two-tail paired Wilcoxon Signed Rank test, with the probability value set at 0.05. The null hypothesis is H0 = “FM-UE scores at T2 and FM-UE scores at T0 follow the same distribution”, H1 = “FM-UE scores at T2 do not follow the same distributions of scores at T0; the distributions are significantly different”. H0 will be rejected if a *p-*value < 0.05 is obtained. This evaluation will be considered together with the expected four-point improvement on average.

To assess if the observed changes in the FM-UE are long-lasting, we will compare with the same test (Wilcoxon Signed Rank, alpha = 0.05) the FM-UE scores at T2 with those acquired at the follow-up (3 months after T2). Another related secondary outcome regards the validation of motor function stability of chronic stroke patients (i.e., no FM-UE improvement during the observation period). We will use a Kruskal-Wallis test with alpha at 0.05 to investigate differences in the FM-UE scores at the three time points of the observation period. We do not expect to reject the null hypothesis for which the three groups are said to come from the same distribution.

Among the most important secondary outcomes is safety and feasibility; for these, descriptive statistics will be provided. One major safety outcome is incidence of epileptic seizures during the intervention period with tDCS, as well as other SAEs. Furthermore, feasibility will be determined by the drop-out rate, usually in clinical trials set to up to 20%.

Important exploratory analyses will focus on the difference between the two interventional phases; such investigation might give an insight on the role of tDCS in the rehabilitation. To test the effect of dose and intervention type on the FM-UE we will use a mixed effects linear model with random effect of subject and fixed effects of session, intervention type and the interaction of the two. If significant results will be observed, we can then build on this initial model by adding more independent variables such as lesion location and time post-stroke. Other analyses will correlate the multimodal data acquired during the three full evaluations (T0, T1, T2), such as corticospinal tract integrity and the TMS evoked potential, with the clinical scales.

Statistical analyses will be performed in a per protocol way using only the data of patients who have finished the study protocol (i.e., drop-out and excluded patients will not be included in the main analyses).

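### The planned T2-versus-follow-up difference test cannot show that FM-UE gains last, and the waiting-group stability test has the same weakness on a test that ignores pairing

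*Protocol article*

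**What the plan says.** The section on primary and secondary outcome measures gives the purpose of the late visit: "To evaluate if the recovery is long-lasting, all patients will be assessed on clinical scales (including FM-UE) 3-months after T2".

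The Statistics section names one analysis for that purpose. It begins "To assess if the observed changes in the FM-UE are long-lasting, we will compare with the same test" and sets the contrast as "the FM-UE scores at T2 with those acquired at the follow-up (3 months after T2"), at alpha 0.05. The test carried over is the primary one: "we will use a two-tail paired Wilcoxon Signed Rank test, with the probability value set at 0.05". The primary null, written for T2 and T0, is "FM-UE scores at T2 and FM-UE scores at T0 follow the same distribution". It is a null of no difference, with no margin.

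The same paragraph then turns to validating motor stability in the waiting group. It plans a Kruskal-Wallis test at 0.05 across the three time points of the observation period and adds: "We do not expect to reject the null hypothesis for which the three groups are said to come from the same distribution".

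The numbers behind both analyses come from the Population Size section: "leads to 30 patients completing the study with 10 starting in the waiting group (2:1 design").

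**The concern.** Whether a gain is long-lasting is a question about follow-up relative to T0: is the patient still better than before treatment? The planned test asks something else, namely whether scores moved between T2 and follow-up.

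This has two consequences.

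- The finding that would favour durability is a failure to reject. Noisier scores or fewer patients at follow-up make that outcome more likely, so weaker data favour the hoped-for answer.
- A small but consistent loss could be significant although most of the gain over T0 remains.

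The stability check has the same structure. The Observational Period section justifies that period by the lack of a control group, and the outcome section uses it as the natural course against which the rehabilitation is compared. The reading of a single-arm result therefore leans on it. Its test also treats three scores from the same 10 patients as three separate groups, so differences between patients, which pairing would remove, stay in the comparison and mask change within patients.

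**Working it through.** **Inputs from the Population Size section.** 30 completers, 10 of them in the waiting group; alpha and beta 0.05; effect size 0.64; SD 4.7; expected gain 4 points.

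**Not in the documents.** The SD of the T2-to-follow-up change, the within-patient correlation and the attendance at follow-up. These are varied below as assumptions.

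**The plan's own figure.** The sample size is stated "for a paired Wilcoxon Signed Rank test considering an alpha and beta of 0.05". I used a noncentral t with effective n = n × 3/π (Wilcoxon efficiency under a normal parent). Effect size 0.64 and power 0.95 give n = 30 one-sided, which matches exactly. Two-sided, it gives 36, with power 0.91 at n = 30; a logistic parent gives 31. The method is therefore adequate for the durability contrast.

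**SDs of change used.**

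- 6.25 = 4 / 0.64, implied by the planning effect size for T0 to T2. With SD 4.7 at each visit, the implied correlation is 1 − 6.25² / (2 × 4.7²) = 1 − 39.06 / 44.18 = 0.12.
- 4.7, which equals 4.7 × √(2 × (1 − 0.5)), that is, correlation 0.5.
- 3, an assumed lower value.

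**Chance that a true 2-point loss (half of 4) is non-significant, n = 30, two-sided 0.05.** Effective n = 30 × 3/π = 28.65; noncentrality = (2 / SD) × √28.65; critical t = 2.05. The simulation applied the Wilcoxon test to integer-rounded scores, 8,000 runs.

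| SD of change | Noncentrality | Non-significant | Simulation |
|---|---|---|---|
| 6.25 | 1.71 | 62% | 62% |
| 4.7 | 2.28 | 41% | 40% |
| 3 | 3.57 | 7% | 7% |

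If only 24 attended follow-up (an assumption), the three figures would be 69%, 51% and 14%.

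**Largest observed mean loss that stays non-significant (paired t approximation), n = 30.** Limit = 2.045 × SD / √30.

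- SD 6.25: 2.33 points, 58% of the 4-point gain.
- SD 4.7: 1.76 points, 44%.
- SD 3: 1.12 points, 28%.

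The limit passes 2 points only when the SD exceeds 2 × √30 / 2.045 = 5.36, or 5.23 after the Wilcoxon efficiency adjustment.

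**Waiting group, n = 10, three visits.** The planned Kruskal-Wallis test was simulated with SD 4.7 at each visit, within-patient correlation 0.5 to 0.9 (assumed) and a linear drift across the visits. A true drift of 4 points, the full treatment target, is detected in about 17 to 24% of trials. A 2-point drift is detected in about 3% or less.

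For comparison, a paired 95% CI for first-to-last change has half-width 2.262 × 4.7 × √(2 × (1 − r)) / √10. That is 3.4 points at r = 0.5 and 1.5 points at r = 0.9.

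**The case against.** **The decision rule is inferred.** A reader might infer that the plan declares a non-significant result to mean long-lasting, and a significant small loss to mean not lasting. It says neither; it says only that the scores will be compared. For the primary outcome, the Statistics section reads the p-value together with the expected four-point gain, so the authors do consider size there. This stands. What remains is that the named test is the only analysis given for durability, that no outcome of it other than non-rejection could support the claim, and that the stability sentence does offer expected non-rejection as validation.

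**The size depends on an unstated SD.** A reader might also infer that losing more than half the gain would routinely go unnoticed. The documents do not support that as a general statement. The 6.25 comes from T0 to T2 and includes variation in treatment response; change over three months after treatment may vary less. Above an SD of about 5.2 to 5.4 the statement holds; at 4.7 or 3 it does not.

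**Much of the remedy is SAP detail.** Confidence intervals and margins are commonly left to the SAP, which is not shown, and their absence from an article is not the point here. The tests and the durability contrast, however, are stated in the article.

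**These are secondary outcomes in a proof-of-concept trial.** True: the primary T0-to-T2 test is unaffected, which limits the weight of the point.

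**Conclusion.** The point holds as one about the choice of analysis. The durability test omits T0, and its only favourable result is a failure to reject. That defect depends on no assumed figure.

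Its size does depend on the SD of the T2-to-follow-up change: a true loss of half the target gain goes undetected in 62% of trials at SD 6.25, 41% at 4.7 and 7% at 3, with all 30 patients attending.

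The stability check is weaker still. Under the assumed SD and correlations, the planned Kruskal-Wallis test would miss an untreated drift equal to the full 4-point target in roughly three to four of every five trials or more (76 to 83%, from 100% minus 24 and 17%). Non-rejection there says little about a plateau.

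This should be corrected before analysis, but it does not threaten the primary result.

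**What to change.** **Durability.** Make the analysis the paired comparison of follow-up with T0, using the same signed-rank test. Report the T2-to-follow-up change with a 95% CI, and claim maintenance only if the CI excludes a loss larger than a margin that the sponsor sets before the data are analysed.

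**Waiting group.** Replace the independent-groups test with a paired or repeated-measures estimate of change with a 95% CI. Call the group stable only if the CI lies within a pre-set margin below 4 points, and otherwise report the result as inconclusive.

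**Cost.** The change is to wording in the analysis plan; it needs no new visits or data. The price is that inconclusive results become likely if scores are noisy. With an illustrative margin of 2 points (not from the documents) and no true loss, 30 patients give a power of 42% at SD 6.25, 65% at SD 4.7 and 96% at SD 3 to show maintenance (one-sided 0.025). The margin must be fixed in advance, since one chosen after seeing the data would carry little weight.

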#### Observational Period

Given the absence of a control group, 10 randomized patients will also do, in addition to the standard protocol, a 3-month observational period prior to the intervention to further validate that the targeted population is in the plateau phase of recovery with a stable level of motor impairment, as suggested in the literature.

Upon recruitment, patients are randomized with a one-to-two distribution into the waiting or the starting group. The waiting group (*n* = 10) corresponds to the patients doing first the observational period and then starting the treatment phase; the starting group (*n* = 20) will directly begin with the treatment phase. The waiting group undergoes an observational period of 3 months prior to beginning the treatment, whereas the starting group begins the treatment immediately. Once the intervention starts, both groups continue the procedure in the same way and receive the same treatment described in the previous paragraphs.

The assignment of patients (waiting or starting group) is performed per center and takes age group (before 50, between 50 and 65, and over 65) and side of impairment into account (53).

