The study outcome is evaluated with the 66-point FM-UE, currently seen as the gold standard measure for motor impairment and function of the upper extremity. Following the suggestions of the SRRR (28), we also instrument this scale with EMG and IMUs to gather further data such as kinematic information, able to better characterize movement quality and functional changes.

The expected primary outcome is a four-point improvement in the FM-UE on average across patients and this is set to be the MCID in this study. Although this is lower than previously suggested (59), it is of note that this suggestion was based on less impaired stroke patients in the acute phase post-stroke, we believe it is an appropriate MCID for the present population of severely impaired patients (60, 61).

The FM-UE, together with the other longitudinal assessed scales and neural correlates will provide important data for understanding the effects of the intervention at a group level and for identifying patients who will potentially benefit from this intervention.

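### The stability check applies Kruskal-Wallis to three repeated FM-UE scores from the same 10 patients; ignoring the pairing favours the hoped-for finding of no change

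*Protocol article*

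**What the plan says.** The Observational Period section states that "10 randomized patients will also do, in addition to the standard protocol, a 3-month observational period prior to the intervention". It gives the absence of a control group as the reason, and the purpose as "to further validate that the targeted population is in the plateau phase of recovery with a stable level of motor impairment". One set of 10 patients is therefore followed over time.

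The Statistics section then says "We will use a Kruskal-Wallis test with alpha at 0.05 to investigate differences in the FM-UE scores at the three time points" of this period, and adds: "We do not expect to reject the null hypothesis for which the three groups are said to come from the same distribution". It gives no power, stability margin or confidence interval for this question.

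The same section handles its other repeated comparisons with methods that respect the patient: a paired Wilcoxon signed-rank test for T0 against T2 and for T2 against follow-up, and a mixed model with a random subject effect for dose and intervention type.

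**The concern.** Kruskal-Wallis assumes independent samples. Here the three samples are the same patients at three visits. If a patient's scores are positively correlated across visits, the change between visits varies less than the test supposes. The test then rejects too rarely, both when nothing changes and when patients drift.

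The direction matters because non-rejection is the result the plan expects. The Introduction justifies the within-subject design partly by expecting no natural recovery, and the observation period is the trial's own check of that premise. The outcome section also lists comparison with the waiting group's natural course as a secondary outcome. A test that seldom rejects gives that premise weak support, whatever the patients do.

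**Working it through.** **Plan's own figure.** None exists for this test. The only sample-size figure, 30 completers, belongs to the primary paired test. Effect size 0.64, alpha 0.05 and power 0.95 reproduce it one-sided with the normal-parent efficiency of the Wilcoxon test. It says nothing about the 10 waiting patients.

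**Inputs from the protocol article.**
- 10 patients (Observational Period); three time points, alpha 0.05 (Statistics).
- Population Size: "considering a mean FM-UE of 15, standard deviation of 4.7 (58) and expected improvement of 4 points". The 4.7 is taken as the total SD of a score at one visit.
- Relevant change (Discussion): "The expected primary outcome is a four-point improvement in the FM-UE on average across patients and this is set to be the MCID".

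**Assumed, because not given.** Within-patient correlation ρ: 0.5 to 0.95, with 0 and 0.115 as checks. Drift is linear over the three visits, and scores are normal and rounded to whole points.

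**Why the test is conservative (raw-score illustration).** With independent groups, the standard error of a difference between two visit means is 4.7 × √(2/10) = 2.10. For the same patients it is 4.7 × √(2(1−ρ)/10): 1.49, 0.94, 0.66 and 0.47 at ρ = 0.5, 0.8, 0.9 and 0.95. Kruskal-Wallis judges change against the first yardstick, in ranks.

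**Simulation, 3,000 trials per cell.** Rejection rates at 0.05, Kruskal-Wallis / Friedman:

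| ρ | no drift | 2 points | 4 points |
|---|---|---|---|
| 0 | 5.1% / 5.5% | 10.6% / 9.6% | 32.3% / 26.2% |
| 0.115 | 2.9% / 4.4% | 8.8% / 10.1% | 28.7% / 27.4% |
| 0.5 | 0.7% / 4.4% | 4.3% / 15.3% | 24.0% / 47.4% |
| 0.8 | 0.07% / 4.5% | 1.2% / 32.3% | 19.7% / 86.1% |
| 0.9 | 0% / 4.2% | 0.6% / 57.9% | 18.1% / 98.8% |
| 0.95 | 0% / 4.5% | 0.4% / 88.1% | 18.5% / 100% |

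Repeat runs shifted entries by about a point (for example, 25.0% for Kruskal-Wallis at ρ = 0.5 and 4 points).

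**Sensitivity, Kruskal-Wallis at a 4-point drift.**
- Total SD 3: 70–76% over ρ 0.5–0.95. Total SD 6: 5–12%.
- Whole gain by the second visit, SD 4.7: 30–36% (Friedman 61–100%).
- Screening score forced below 20, with 4.7 as the between-patient SD before that limit and within-patient SD 1, 2, 3: visit SD falls to about 3.8–4.4, and detection is 41%, 32%, 28% (Friedman 100%, 90%, 57%).
- A larger drift of 5.25 points, SD 4.7: 46–50%.

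**What an estimate would give.** The 95% CI half-width for last minus first visit is 2.262 × 4.7 × √(2(1−ρ)) / √10, that is 3.4, 2.1, 1.5 and 1.1 points at ρ = 0.5, 0.8, 0.9 and 0.95.

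**The case against.** A reader might infer that drift would almost never be found and that a finding of stability is close to guaranteed. The documents do not support that. It fits drifts of about 2 to 3 points with high correlation at SD 4.7. At 4 points, detection is about one in five, and it rises towards 40% if the entry limit narrows the spread, and further if the SD is smaller still.

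The size of the loss also rests on a correlation that the protocol does not give. The only paired figure in the plan points the other way: a 4-point change at effect size 0.64 implies a change SD of 4/0.64 = 6.25, hence ρ = 1 − 6.25²/(2 × 4.7²) = 0.12, where Kruskal-Wallis loses almost nothing. That figure concerns T0 to T2, across treatment, and need not carry over to an untreated period. The plan's own expectation of a stable level of impairment suggests a higher correlation. Still, the objection stands as a limit on the stated size.

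Two further points stand. Small numbers are part of the problem: even Friedman finds a 4-point drift only 47% of the time at ρ = 0.5, so exchanging one test for another while still reading non-rejection as stability would not be enough. And the check is secondary: the plateau is assumed beforehand, with reference to the literature, and the observation period is meant to add support. It would be wrong to infer that the primary T0–T2 test is invalid; it is correctly paired.

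None of this makes an independent-groups test suitable for repeated scores.

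**Conclusion.** The point holds as a stated wrong choice of test for a secondary outcome. With total SD 4.7, linear drift and an assumed correlation of 0.5–0.95, the true size is below 1% instead of 5%. A 2-point drift is detected about 0.4–4% of the time (Friedman 15–89%) and a 4-point drift about 17–24% (Friedman 46–100%). On those assumptions the plan would miss a spontaneous gain as large as its own MCID roughly four times in five.

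The existence and direction of the error are firm for any appreciable positive correlation. Its size is not: it depends on the spread of scores in patients below 20 points, on the shape of the drift, and on the missing correlation. Non-rejection by this test should not be reported as validation of the plateau.

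**What to change.** In the Statistics section or the SAP, replace Kruskal-Wallis with a repeated-measures method: the Friedman test, or a mixed model with visit as fixed and patient as random effect.

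Base the stability statement on the mean first-to-last change with its 95% CI, judged against a margin that is fixed in advance and lies below the 4-point MCID. State that non-rejection alone will not be read as stability, and that a CI reaching past the margin will be reported as inconclusive. With 10 patients that is a real possibility at lower correlations (half-width 3.4 points at ρ = 0.5).

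The cost is a sentence or two and agreement on a margin before the data are examined. No new data, visits or patients are needed, and the primary analysis is unchanged.
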